### Interim analyses {21b}

A blinded interim analysis will be conducted at 30% of enrollment, of which 141 participants would be available for efficacy comparison (the number of survival in cerebral malaria in each arm of the study). Using a conservative Haybiltte-Peto [21] repeated assessments criterion, the stopping early will be recommended at *p* < 0.001 and final significance at *p* < 0.05.

The results will be made accessible to the pharmacologist (unblinded) and the Data Safety and Monitoring Board (DSMB). Early stopping consideration will be on safety concerns to adverse events more than 50% in the study.

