#### Secondary outcomes

Number of patients that regained full consciousness as measured by GCS/MGCS of > 11 for children > 5 years or Blantyre Coma Scale of > 3 in children < 5 years at 12 and 24 h post-randomization.Number of patients with asexual form of malaria parasite present or absent at 12 and 24 h post-randomization.Number of patients that achieved fever defervescence (attainment and sustenance of axillary temperature of < 37.5 °C) at 12 and 24 h post-randomization.Parasite density at 12 and 24 h post-randomization.Number of patients with neurologic deficits at the fourth week (day 29) post-intervention in each of the arms. Neurology deficit is defined as the presence of impaired cognitive, motor or cranial nerve palsy and or persistence of convulsions.Time to convert to a full dose of enteral artemisinin-based combination therapy.The side effect profile (adverse events and serious adverse events) of medication in each arm of study: (i) solicited side effects include hypoglycaemia, arrhythmia, thrombocytopenia, tinnitus and anaemia; (ii) unsolicited adverse events as reported by patients post-randomization; (iii) random plasma glucose will be measured 6 hourly until 48 h after parasite clearance. Hypoglycaemia will be corrected with 2-4 ml/kg of 10% D/W and maintenance with glucose infusion at 6–8 mg/kg/min until euglycaemic; (iv) electrocardiography will be recorded before the administration of anti-malaria and 4 h after an intervention. The QT and RR will be measured by software and checked manually. Bazett’s formula will be used to correct the QT interval (QTc = QT/RR**0.5). Prolonged QT interval managed as per hospital protocol; (v) haematocrit, serum ferritin, platelet count and erythrocyte sedimentation rate will be monitored at baseline and 24 h and 48 h post-randomization.Plasma levels of inflammatory markers including C reactive protein, procalcitonin, lactate dehydrogenase and interleukin 6 at baseline, 24 h, and 48 h. Inflammatory markers and cytokine are included to assess a possible ‘cytokine storm’ in the course of parasite clearance.

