### Sample size {14}

The sample size for this study was calculated using the G*Power calculator, based on the reported outcomes of cerebral malaria with quinine monotherapy (23.0%) and a dual quinine and artesunate combination therapy (12.5%) [10, 18–20]. Going for a difference of 23.0 to 12.5%, a sample size of 470 participants is required accounting for a 10% attrition rate at 80% power of a 2-sided alpha level of significance of 0.05. Based on 1:1 allocation, the treatment arm will have 235 participants and the same number for the control arm. The details of the selected studies for the sample size calculation are shown in a supplementary document as a table.

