#### Composition of the data monitoring committee, its role, and reporting structure {21a}

The Data Safety and Monitoring Board DSMB will consist of a multi-disciplinary team of five professionals from the University College Hospital Ibadan. They will have oversight monitoring and safety checks on the data quality and interim analysis of the trial data. They will ensure conformity to the trial protocol. In the event of the inferiority of the primary and secondary outcomes of the trial compared with the standard of care and in the event of worse adverse reactions in the experimental arm, the trial would rely upon the extensive data safety review of the DSMB and the clinical pharmacologist to evoke a stopping rule on the trial.

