#### Adverse event reporting and harms {22}

All participants in this trial will be monitored for medication side effects and adverse events. An adverse event (AE) is any untoward medical occurrence which happens to a participant on a trial. All AEs will be reported in the case report form (CRF) regardless of suspected causality. Medidata rave will be used for reporting of AEs. Serious adverse events (SAEs) include fatal medical occurrences, life-threatening, that require or prolong hospitalization or cause congenital anomaly or permanent or significant disability or incapacity. All SAEs will be reported to the sponsor, Local Health Research Ethics and DSMB, and Trial Steering Committee within 24 h.

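### The only numeric safety criterion, adverse events above 50% in the study, is undefined and not compared between arms, so it does not measure harm from the added quinine

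*Protocol article*

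**What the plan says.** All references are to the protocol article.

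- **Interim analyses {21b}.** "A blinded interim analysis will be conducted at 30% of enrollment, of which 141 participants would be available for efficacy comparison", namely survival in each arm. The efficacy boundary is p < 0.001. On safety the section says: "Early stopping consideration will be on safety concerns to adverse events more than 50% in the study". Results go to the DSMB and to the unblinded pharmacologist.
- **Adverse event reporting and harms {22}.** An adverse event is any untoward medical occurrence, and "All AEs will be reported in the case report form (CRF) regardless of suspected causality". Fatal events are serious adverse events (SAEs). SAEs reach the DSMB within 24 h.
- **Secondary outcomes.** The "solicited side effects include hypoglycaemia, arrhythmia, thrombocytopenia, tinnitus and anaemia". The concomitant care section {11d} permits treatment for severe anaemia and hypoglycaemia during the trial.
- **Data monitoring committee {21a}.** A second basis for stopping: "In the event of the inferiority of the primary and secondary outcomes of the trial compared with the standard of care", followed by an *and* and the case of worse adverse reactions in the experimental arm, the trial relies on safety review by the DSMB and the pharmacologist to invoke a stopping rule. No boundary is given.
- **Sequence generation {16a}, concealment {16b} and implementation {16c}.** The same pharmacologist generates the sequence, is called by centres at each enrolment, delivers the treatment boxes and implements the randomization.

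**The concern.** The safety question in this trial is whether adding quinine to artesunate harms children. That is a comparison between arms. A threshold on the pooled share of children with any event answers a different question: how often comatose children with malaria have anything untoward recorded. The pooled share rises with the background rate and dilutes an excess confined to one arm by about half.

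Two errors can follow. A large excess in the dual arm may leave the criterion unmet, and background events may meet it when the drugs do not differ. The second basis for stopping, in {21a}, is comparative but unquantified, and the protocol does not say how the two fit together.

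There is also a question of who sees the results. By-arm interim survival goes to the person who controls allocation and also takes part in invoking a stopping rule, and no need for this is stated.

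**Working it through.** **The plan's own figure.** The interim is at 30% of 470: 0.30 × 470 = 141, as stated. With 1:1 allocation that is about 71 control and 70 dual-arm children. The 50% threshold has no derivation to reproduce.

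**Reading used.** More than 50% of participants with at least one event means at least 71 of 141, since 0.5 × 141 = 70.5. The protocol does not say whether it counts participants or events, so this reading is an assumption. All event rates below are assumed too, because the protocol gives none.

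**1. Unequal arms.** Let X be Binomial(71, p_control) + Binomial(70, p_dual). P(X ≥ 71) comes from convolving the two distributions.

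| Control | Dual | P(criterion reached) |
|---|---|---|
| 30% | 60% | 0.10 |
| 20% | 60% | 0.004 |
| 70% | 50% | 0.993 |

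Hand check of the first row: the mean is 71 × 0.30 + 70 × 0.60 = 63.3 and the variance is 71 × 0.21 + 70 × 0.24 = 31.7, so the SD is 5.63. Then (70.5 − 63.3)/5.63 = 1.28, an upper tail of 0.10.

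For the same 30% and 60%, exact enumeration of a two-sided between-arm test at 0.05 gives power 0.950 (chi-squared) or 0.948 (Fisher). In the second row, the expected counts of about 14/71 and 42/70 give a Fisher p of about 1 × 10⁻⁶, yet the criterion is almost never reached. In the third row the dual arm is the safer one and the criterion is almost always reached.

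**2. Equal arms (no drug harm).** P(Binomial(141, p) ≥ 71):

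| True event rate in both arms | P(criterion reached) |
|---|---|
| 40% | 0.008 |
| 45% | 0.12 |
| 50% | 0.50 |
| 55% | 0.88 |
| 60% | 0.992 |

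The result turns on whether the background rate lies below about 45% or above about 55%.

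**3. Is a rate near 50% plausible?** Deaths count as SAEs. If a share m die, the share of survivors with any event that brings the total to 50% is (0.50 − m)/(1 − m).

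- At m = 23% (the higher planning rate in the sample size section): 0.27/0.77 = 35% of survivors.
- At m = 35% (the mortality in the research problem section): 0.15/0.65 = 23% of survivors.

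Alternatively, with no deaths counted, five independent solicited events at about 13% each suffice: 1 − 0.5^(1/5) = 0.129. So 50% is within reach, but the protocol does not establish it.

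**4. Does the p < 0.001 boundary fill the gap for deaths?** With 16/71 control deaths (22.5%), 34/70 in the dual arm gives p = 0.0012 (chi-squared) or 0.0015 (Fisher), which does not cross. Crossing takes 35/70 by either of those tests, or 36/70 with a continuity-corrected chi-squared. An excess of 49% against 23% mortality would therefore not meet it.

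**The case against.** The strongest reply is that the 50% figure is only one part of safety oversight. Under {21a} the DSMB acts on worse adverse reactions in the experimental arm, under {22} it receives every SAE within 24 h, and detailed harm boundaries usually sit in a charter that an article would not reproduce. This stands in part. A reader might infer that harm in one arm could not be noticed at all. The protocol does not support that, because a comparative route exists. But that route has no stated boundary, and it does not repair the numeric criterion that the article does state.

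Three other stronger readings also go too far.

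- **Malaria alone will push events past 50%.** No event rate is given. Events are recorded after randomization, and the blood indices and glucose have baseline values, so abnormalities present at entry are not clearly adverse events. The equal-arm table shows how far the answer depends on the assumed rate.
- **Crossing 50% stops the trial.** The text speaks of considering early stopping. The probabilities above are chances of prompting that consideration, not of stopping.
- **Excess deaths alone cannot qualify under {21a}.** The *and* can be read as joining two conditions or as listing two separate triggers. It is ambiguous, not clearly conjunctive.

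On the pharmacologist, it is fair to say that this person is already unblinded and that allocation follows a generated sequence with numbered boxes. No actual bias is shown. The point is only that the exposure serves no stated purpose and is easily avoided.

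**Conclusion.** The concern holds in a limited form and should be fixed. The criterion lacks an arm, a comparator, a severity and a counting unit. On its natural, pooled and all-cause reading it does not measure harm from the added quinine. That conclusion needs no particular background rate: the criterion is reached in about 10% of trials at 60% against 30%, where a direct comparison succeeds in about 95%, and in about 99% of trials when the dual arm is the better one.

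Whether background events would reach it without any drug effect is uncertain (0.008 to 0.99 over assumed rates of 40% to 60%). The figures rest on counting participants with any event, on the assumed rates, and on 71 and 70 children per arm at the interim. Separately, {21a} and {21b} give two unreconciled bases for stopping, and by-arm interim results go to the person who controls allocation.

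**What to change.** 1. In {21b}, replace the pooled 50% criterion with DSMB review by arm of deaths, children with any SAE, and children with each solicited event. Judge these against a non-binding between-arm harm guideline whose level the DSMB sets in its charter.
2. Reconcile {21a} with {21b}, so that an excess of deaths or an excess of SAEs in the dual arm is each sufficient to prompt consideration of stopping.
3. Keep p < 0.001 as the boundary for benefit.
4. Send by-arm interim results to the DSMB only, not to the pharmacologist who generates the sequence and releases treatment. Emergency unblinding of single patients under {17b} is unaffected.

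The cost is wording in two sections and the charter. There is a small chance of a DSMB review or pause with no true harm, governed by the level the DSMB chooses. A non-binding harm guideline does not inflate the type I error for efficacy. The trial status section says the trial is not recruiting, so the change can precede enrolment.

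### The only numeric safety trigger is an absolute 50% adverse-event level with no arm, comparison, seriousness or counting unit, so it follows background illness more than harm from adding quinine

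*Protocol article*

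**What the plan says.** All references are to the protocol article.

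- **Interim analyses {21b}:** "A blinded interim analysis will be conducted at 30% of enrollment", which is 141 children. Results go to the unblinded pharmacologist and the Data Safety and Monitoring Board (DSMB). On safety, the section says: "Early stopping consideration will be on safety concerns to adverse events more than 50% in the study". It gives no other safety figure.
- **Adverse event reporting and harms {22}:** "An adverse event (AE) is any untoward medical occurrence which happens to a participant on a trial", and "All AEs will be reported in the case report form (CRF) regardless of suspected causality". Deaths are included: "Serious adverse events (SAEs) include fatal medical occurrences, life-threatening, that require or prolong hospitalization".
- **Secondary outcomes:** "solicited side effects include hypoglycaemia, arrhythmia, thrombocytopenia, tinnitus and anaemia".
- **Relevant concomitant care {11d}:** treatment is allowed for septicaemia, severe anaemia, milder acute kidney injury and hypoglycaemia, so these are foreseen in the disease itself.
- **Composition of the data monitoring committee {21a}:** if reactions are worse on the experimental arm, the DSMB's safety review, with the pharmacologist, may invoke a stopping rule. No threshold is given, and the 50% figure is not mentioned.

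**The concern.** The safety question in this trial is comparative: does adding quinine to artesunate harm children? An absolute level across all participants does not address it. Every child enters with impaired consciousness, and several solicited events are also complications of severe malaria. Under the article's own definitions, background illness alone could carry the share past 50% in both arms. Conversely, with 1:1 allocation the overall share is roughly the mean of the two arms, so a low control rate can hold it below 50% while the dual arm has a large excess.

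At stake are a DSMB discussion of stopping prompted by the disease rather than the drug, and a formal trigger that stays silent when the comparison the board needs is unfavourable.

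**Working it through.** **Inputs from the article.** Total N = 470, 1:1 allocation, interim at 30%, trigger above 50%. Rates mentioned: 35% (Abstract and Research problem) and 23.0% v 12.5% (Sample size {14}). The article gives no adverse-event rates and no derivation of the 50%.

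**Plan's own figure.** 0.30 × 470 = 141, which reproduces the stated interim size. That is about 70 and 71 per arm. More than 50% of 141 means at least 71 children.

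**Assumed unit.** Children with at least one adverse event. The article does not say whether children or events are counted.

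**1. How close deaths alone bring the share to 50%.** Deaths count as adverse events.
- If mortality is 35%: (0.50 − 0.35)/0.65 = 0.15/0.65 = 23% of survivors need any event.
- If mortality is 23%: (0.50 − 0.23)/0.77 = 0.27/0.77 = 35% of survivors.

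The Research problem section calls the 35% morbidity and mortality together, and the sample-size section does not spell out that 23.0% is mortality. Both are therefore illustrations.

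**2. No drug effect.** P(X ≥ 71), X ~ Binomial(141, q):

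| True share q, both arms | P(trigger) |
|---|---|
| 40% | 0.8% |
| 45% | 11.7% |
| 50% | 50% |
| 55% | 88% |
| 60% | 99.2% |
| 70% | >99.9% |

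**3. Real excess in the dual arm.** P(X + Y ≥ 71), X ~ Binomial(70, pc), Y ~ Binomial(71, pt), by exact convolution. For 20% v 60% the expected overall share is (70 × 0.20 + 71 × 0.60)/141 = 56.6/141 = 40%.

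By-arm power at two-sided 5% with n = 70.5 per arm is Φ{[|pt − pc| − 1.96√(2p̄(1 − p̄)/n)] / √[(pc(1 − pc) + pt(1 − pt))/n]}, where p̄ is the mean of the two shares. For 25% v 50%: (0.25 − 1.96 × 0.0815)/0.0788 = 1.14, and Φ(1.14) = 87%.

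| Control v dual, any event | Trigger fires | By-arm comparison detects |
|---|---|---|
| 20% v 60% | 0.5% | >99% |
| 25% v 50% | 0.1% | 87% |
| 30% v 60% | 11% | 95.5% |

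Both tables use the same unit, so they can be compared directly.

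**4. If only the dual arm was meant.** The trigger is then at least 36 of 71. With no drug effect it fires in 80% of trials at a 55% share and 96% at 60%. It catches 20% v 60% in 96%, but it fires equally often at 60% v 60%, because the control rate plays no part.

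**The case against.** Much of the case on the other side stands.

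- **The DSMB is not blind to an excess.** A reader might infer from the 50% rule that a real excess in the dual arm would produce no signal. The article does not support that. The data monitoring section gives the board a comparative remit, serious events reach it within 24 hours, and the pharmacologist can unblind for a life-threatening event or signs of quinine toxicity. What is missing is a threshold for that remit and any link to the 50% figure.
- **Pooling is not stated.** An all-participant share is the plain reading, but the sentence does not say so. The firm defect is an undefined, non-comparative rule. Step 4 shows that the dual-arm reading does not rescue it.
- **The trigger prompts consideration only.** It does not oblige the board to stop.
- **A near-zero chance of firing for one harm would mislead.** Taken alone, a harm at 5% v 20% never brings the overall share to 50%, but the rule counts all adverse events. Adding that harm independently to a common background share gives arm shares of 1 − (1 − b) × 0.95 and 1 − (1 − b) × 0.80. The trigger then fires in about 28% of trials at b = 40%, 68% at 45%, 93% at 50% and 99.5% at 55%. Set against step 2, most of that movement comes from the background.
- **A journal article condenses.** Detailed stopping criteria can sit in a DSMB charter. But this sentence does fix a criterion, and a charter that follows it inherits the problem.

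**Conclusion.** The point holds as a should-fix. As written, the only numeric safety trigger is absolute, undefined as to arm and unit, and indifferent to cause, so it responds mainly to how common events are overall. With no drug effect its chance of firing rises from 12% to 99% as the assumed share goes from 45% to 60%. For dual-arm excesses of 25 to 40 percentage points it fires in 0.1% to 11% of trials, where a by-arm comparison detects 87% or more.

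These figures assume one look at 141 children, children with at least one event as the unit, and event shares that the article does not supply. If the true share under standard care were 40% or lower, false alarms would be rare (0.8%), but the trigger would still be non-comparative.

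The finding does not extend to saying that harm would go unmonitored or that a stop would be forced. It says that the numeric rule and the board's comparative remit differ and are not reconciled.

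**What to change.** In Interim analyses {21b}, replace the absolute 50% trigger with a comparative one, and cross-refer to the data monitoring section {21a} so that the two state a single rule. For example:

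*At each DSMB review, the number and share of children with at least one serious adverse event, and with each solicited event, will be tabulated by arm, with the dual-minus-control risk difference and 95% confidence interval. Consideration of stopping for safety will rest on an excess in the dual arm. The DSMB will set the events and threshold in its charter before the first review.*

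Risk differences with 95% confidence intervals are already the method for categorical outcomes in Statistical methods {20a}. The interim is called blinded and promises by-arm figures only for survival, so the text should also say that the DSMB receives safety tables by arm.

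**Cost.** A few sentences here and in the charter, with no change to sample size. If the board flagged whenever the interval lay wholly above zero, the false-flag rate at 70 per arm would be about 3% per measure per look. For three independent measures at one look that is about 1 − 0.97³ = 9%, and more over repeated looks. This is tolerable for an advisory flag, and the board can choose a stricter threshold. Power for rare harms stays low: 5% v 10% at 70 per arm would be flagged about 20% of the time, so clinical review of individual serious events remains necessary. The article says the trial is not yet recruiting, so the change can be made before any data accrue.

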## Methods for additional analyses {20b}

Subgroup analysis will be performed using variables such as geopolitical region, gender, socio-economic status of parents and care provider, level of education, and occupation. The primary outcome, survival in each study arm, will be analysed in each subgroup analysis.

### Methods in analysis to handle protocol non-adherence and any statistical methods to handle missing data {20c}

The result of the study will be analysed per protocol. The number of participants with missing data will be clearly stated, and the missing items will be mentioned.

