**Methods:**

This is a parallel multi-site randomized controlled superiority triple blinded trial consisting of intravenous artesunate plus quinine and a control arm of intravenous artesunate only. Eligible and assenting children aged 6 months to 17 years will be recruited from 4 tertiary hospitals by random selection from the list of tertiary hospitals in Nigeria. Participants will be randomized and assigned in parallel into two arms using random numbers generated from GraphPad Prism (version 9) by a clinical pharmacologist who has no link with the investigators, the patients, or the statistician. The primary measurable outcome is survival at 12, 24, and 48 h post-randomization. A composite secondary outcome consists of the number of children that regained consciousness, parasitaemia and defervescence at 12 and 24 h post-randomization and haematological and inflammatory markers at 24 and 48 h post-randomization. Adverse events both solicited and unsolicited are recorded all through the study post-randomization. The study is approved by the State Research Ethics Review Committee. Data analysis will be performed in GraphPad Prism version 9.

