#### Criteria for discontinuing or modifying allocated interventions {11b}

Participants who regained full recovery after initial treatment.Participants who also wish to exit after due counselling.Participants with intractable hypoglycaemia despite maintenance at 12.5% glucose.Participants with dysrhythmias will be unblinded.Participants who develop commodities of severe malaria that could confound the measurable outcomes such as uraemic encephalopathy.Participant with a new disease besides cerebral malaria or updated clinical history related to exclusion criteria.

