### Outcomes {12}

#### The primary outcome

The primary outcome is survival measured at 48 h post-randomization.

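### Per protocol is the only analysis population named for a superiority trial on 48 h survival, and the listed reasons for stopping or changing treatment can make that set informative, with a bias of uncertain direction

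*Protocol article*

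**What the plan says.** The Abstract (Methods) describes a "parallel multi-site randomized controlled superiority triple blinded trial". The Outcomes section {12} states: "The primary outcome is survival measured at 48 h post-randomization".

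Section {20c}, which covers non-adherence and missing data, names the analysis: "The result of the study will be analysed per protocol". It does not define the per-protocol set. On missing data it says only: "The number of participants with missing data will be clearly stated, and the missing items will be mentioned". The statistical methods section {20a} names tests and models but no population, and intention-to-treat does not appear anywhere.

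Section {11b} gives the criteria for discontinuing or modifying the allocated treatment. They include "Participants with intractable hypoglycaemia despite maintenance at 12.5% glucose", the statement "Participants with dysrhythmias will be unblinded", and complications of severe malaria "that could confound the measurable outcomes such as uraemic encephalopathy". Also listed are a new disease or later-found history bearing on the exclusion criteria, a wish to leave, and full recovery after initial treatment.

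The secondary outcomes list hypoglycaemia and arrhythmia among the solicited side effects. Section {17b} provides for unblinding when features of quinine toxicity appear. Only the experimental arm receives quinine; the control arm receives 10% dextrose in its place.

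**The concern.** A superiority claim on mortality rests on comparing the groups that randomisation formed. A per-protocol set selects children on what happened after randomisation. Here the events that could drive the selection are related to prognosis, and some may be related to the treatment: hypoglycaemia and arrhythmia are side effects the protocol itself looks for, and quinine is given in one arm only. If children who stop for these reasons die more often than the rest and are left out more often from the dual arm, its survival is overstated. A neutral or harmful combination could then look beneficial.

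This is more than detail left to an analysis plan. The protocol makes a positive choice of population, and the choice does not suit the design.

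**Working it through.** **Planning figures.** The Sample size section {14} uses 23.0% against 12.5%, two-sided 5% significance, 80% power, 10% attrition and 235 children per arm. The pooled two-proportion formula without continuity correction gives 207 per arm. Dividing by 0.9 gives 230 per arm, or 460 in total, close to the stated 470.

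**Model with exclusions in the dual arm only.** Let m be the true mortality in both arms (no effect), f the share of the dual arm excluded and q the mortality among those excluded. I take m = 0.23 from the sample size section, reading that figure as mortality. The documents give neither f nor q; both are assumptions.

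- Apparent dual-arm mortality: (m − f·q)/(1 − f).
- Spurious difference: d = m minus that value.
- Two-sided rejection rate: Φ((d − 1.96·se0)/se1) + Φ((−d − 1.96·se0)/se1). Here se0 is the pooled and se1 the unpooled standard error, with 235 and 235(1 − f) children. The first term is false superiority, nominally 2.5%.

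Example with f = 0.10 and q = 0.70: (0.23 − 0.07)/0.90 = 17.8%, so d = 5.2 points. With se0 = 0.0383 and se1 = 0.0380, the first term is Φ(−0.60) = 0.274.

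| Excluded, dual arm only | Mortality among excluded | Apparent dual v control | False superiority | Two-sided rejection |
|---|---|---|---|---|
| 2% | 50% | 22.4% v 23.0% | 3.5% | 5.2% |
| 5% | 50% | 21.6% v 23.0% | 5.5% | 6.5% |
| 10% | 50% | 20.0% v 23.0% | 11.6% | 11.9% |
| 10% | 70% | 17.8% v 23.0% | 27.4% | 27.5% |
| any | 23% | 23.0% v 23.0% | 2.5% | 5.0% |
| 10% | 10% | 24.4% v 23.0% | 1.0% | 6.5% |

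The last two rows show no bias when the excluded children resemble the rest, and reversed bias when they do better.

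**Exclusions in both arms.** With 8% of the dual arm and 5% of the control arm excluded, at 50% mortality: (0.23 − 0.04)/0.92 = 20.7% against (0.23 − 0.025)/0.95 = 21.6%. Two-sided rejection is 5.6%.

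**Recovered survivors removed as well.** Full recovery is on the same list. If a share r of each arm is removed as recovered survivors, apparent mortality is (m − f·q)/(1 − f − r). Take f = 5% and q = 50% in the dual arm, none in the control arm, and r = 10% in the control arm (all assumed):

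- r = 15% in the dual arm: 0.205/0.80 = 25.6% against 0.23/0.90 = 25.6%. The biases cancel.
- r = 20% in the dual arm: 0.205/0.75 = 27.3% against 25.6%. The bias now runs against the dual arm, and false superiority is 0.9%.

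**Analysed as randomised.** With no true effect, the expected difference is 0. At the planned rates, power is 84.8% with 470 children and 80.9% with 423 (470 × 0.9).

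**The case against.** The strongest reply is that exclusion is inferred. Section {11b} concerns stopping or changing treatment; it does not say that these children leave the analysis, and the dysrhythmia item mentions only unblinding. A child whose treatment was stopped under a rule of the protocol could be counted as treated according to protocol. This stands as a limit: exclusion is the ordinary reading of a per-protocol analysis, but it is not written. It does not rescue the plan, because an undefined set leaves the choice open, including for children whose allocation has been revealed.

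A reader might go further and infer that the plan is bound to favour the dual arm. The documents do not support that. Full recovery is on the same list, and removing survivors works the other way. Side effects are to be recorded in each arm, treatment of hypoglycaemia is permitted without restriction to one arm, and uraemic encephalopathy is presented as a complication of malaria, not of quinine. Hypoglycaemia and arrhythmia can therefore arise in controls too. What remains is a plausible excess in the arm that receives quinine.

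It is also fair to object that the larger figures depend on chosen exclusion rates, and that several reasonable scenarios leave the error rate close to nominal.

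**Conclusion.** The stated rule is wrong for this design and should be changed. Per protocol is the only population named in a superiority trial on 48 h survival, and the protocol's own list supplies prognostic reasons by which children can leave it. The randomised comparison is then not protected.

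Neither direction nor size is established. Under the assumptions shown, two-sided rejection with no true effect runs from 5.2% to about 27% when exclusions fall on the dual arm only and those excluded die more often than the rest. It is near 5% when exclusions are few or similar in both arms, and the bias cancels or reverses when recovered survivors are removed more often from the dual arm. These figures show what the rule permits; they do not forecast this trial. An uncertain direction is a further reason to analyse as randomised, since no correction could be fixed in advance.

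**What to change.** In section {20c}, make intention-to-treat the primary analysis: every randomised child is analysed in the assigned arm, whatever the treatment received, discontinuation or unblinding. Add that vital status at 48 h is sought for all, including children who stop treatment and, where consent allows, those who leave the trial. Define a per-protocol set and keep it as a labelled sensitivity analysis. In section {11b}, state that stopping or changing treatment does not end outcome collection.

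The cost is mainly wording. Survival at 48 h is already in the participant timeline, but children who leave may need tracing and a consent provision. Non-adherence may dilute the estimate slightly. The sample size stays at 470 and no clinical rule is altered. The Trial status section says the trial is not recruiting, so the change can be made before any result is known.
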